**ABBREVIATED FORM**

|            |                                                                    |
|------------|--------------------------------------------------------------------|
| A1         | First Annular Pulley                                               |
| COPM       | Canadian Occupational Performance Measure                          |
| DASH       | Disabilities of the Arm, Shoulder and Hand Outcome Measure         |
| DIPJ       | Distal Interphalangeal Joint                                       |
| EDC        | Extensor Digitorum Communis                                        |
| EDM        | Extensor Digiti Minimi                                             |
| EIP        | Extensor Indicis Proprius                                          |
| FDP        | Flexor Digitorum Profundus                                         |
| FDS        | Flexor Digitorum Superficialis                                     |
| MCPJ       | Metacarpophalangeal Joint                                          |
| MCPJBG     | Metacarpophalangeal Joint Blocking Group                           |
| PIPJ       | Proximal Interphalangeal Joint                                     |
| QuickDASH  | Quick-Disabilities of the Arm, Shoulder and Hand Outcome Measure   |
| RM         | Relative Motion                                                    |
| RME Splint | Relative Motion Extension Splint                                   |
| RMF Splint | Relative Motion Flexion Splint                                     |
| RMG        | Relative Motion Group                                              |
| ICF        | International Classification of Functioning, Disability and Health |
| IPJ        | Interphalangeal Joint                                              |
| SST        | Stages of Stenosing Tenosynovitis                                  |
| TF         | Trigger Finger                                                     |
| VAS        | Visual Analog Scale                                                |

**RESEARCH SYNOPSIS**

|                          |                                                                                                                                                                                                                                                                                                                                                                                                                                                                                                                                                                                                                                                                                                                                                                                                                                                                                                                                                                                     |
|--------------------------|-------------------------------------------------------------------------------------------------------------------------------------------------------------------------------------------------------------------------------------------------------------------------------------------------------------------------------------------------------------------------------------------------------------------------------------------------------------------------------------------------------------------------------------------------------------------------------------------------------------------------------------------------------------------------------------------------------------------------------------------------------------------------------------------------------------------------------------------------------------------------------------------------------------------------------------------------------------------------------------|
| Study title              | A Randomized Comparative Trial of Relative Motion Splint versus Metacarpophalangeal Joint Blocking Splint in the Management of Trigger Finger                                                                                                                                                                                                                                                                                                                                                                                                                                                                                                                                                                                                                                                                                                                                                                                                                                       |
| Study Population         | Patients who are diagnosed with TF involving the A1 pulley by a surgeon in the Orthopaedic Clinic, Hospital Sultan Haji Ahmad Shah, Temerloh, Pahang; satisfy the inclusion criteria; and referred for TF management at the Occupational Therapy Unit of this same public hospital during the period 1 January 2022 – 31 December 2024.                                                                                                                                                                                                                                                                                                                                                                                                                                                                                                                                                                                                                                             |
| Study Design             | A randomized comparative trial study. with random assignment of participants will be randomized assign into Relative Motion Group (RMG) that receives RM splint, or Metacarpophalangeal Joint Blocking Group (MCPJBG) that receives MCPJ blocking splint. Splint wear full time for 6 weeks                                                                                                                                                                                                                                                                                                                                                                                                                                                                                                                                                                                                                                                                                         |
| General Objective        | To compare the effectiveness of RM and MCPJ blocking splints in terms of sign and symptoms, hand function, occupational performance, and perception of splint wearability (comfort and satisfaction) after six weeks of TF management.                                                                                                                                                                                                                                                                                                                                                                                                                                                                                                                                                                                                                                                                                                                                              |
| Specific Objectives      | 
 
1) To compare the effectiveness of RM splint and MCPJ blocking splint on TF severity after six weeks of TF management.
 
2) To compare the effectiveness of RM splint and MCPJ blocking splint on pain after six weeks of TF management.
 
3) To compare the effectiveness of RM splint and MCPJ blocking splint on finger triggering after six weeks of TF management.
 
4) To compare the effectiveness of RM splint and MCPJ blocking splint on hand function after six weeks of TF management.
 
5) To compare the effectiveness of RM splint and MCPJ blocking splint on occupational performance after six weeks of TF management.
 
6) To compare the effectiveness of RM splint and MCPJ blocking splint on comfort after six weeks of TF management.
 
7) To compare the effectiveness of RM splint and MCPJ blocking splint on satisfaction after six weeks of TF management.
 
 |
| Study endpoints/outcomes | 
 
1) There is a difference in terms of severity staging of TF.
 
2) There is a difference in terms of pain.
 
3) There is a difference in terms of finger triggering.
 
4) There is a difference in terms of hand function.
 
5) There is a difference in terms of occupational performance.
 
6) There is a difference in terms of comfort.
 
7) There is a difference in terms of satisfaction.
 
                                                                                                                                                                                                                                                                                                                                                                                                                                                                                         |
| Sample Size              | 42 participants                                                                                                                                                                                                                                                                                                                                                                                                                                                                                                                                                                                                                                                                                                                                                                                                                                                                                                                                                                     |
| Study Duration           | 1 January 2022 - 31 December 2024                                                                                                                                                                                                                                                                                                                                                                                                                                                                                                                                                                                                                                                                                                                                                                                                                                                                                                                                                   |

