### 3.5 Withdrawal criteria

Participants can choose to withdraw at any time. Participants may be withdrawn if the investigator deems that it is detrimental or risky for the subject to continue. Withdrawn subjects will not be replaced by a new participant as we have already included the dropout rate (10%) into our sample size calculation.

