### 3.6 Sample Size

A sampling of convenient method will be used to select eligible patients.

A prior TF research study (Teo et al. 2019) had reported that the result of pain score for pre-treatment = 4.65 (SD 2.39) and post-treatment = 3.40 (SD 2.44). G\*Power was used to compute statistical power analyses. Cohen-d effect size is 0.5175152.

Given Cohen-d effect size needs to be converted into Cohen-f effect size in order to determine the sample size of this study for two ways ANOVA, therefore, after converting digitally, the Cohen-f effect size is 0.259.

This proposed study will need 32 participants when a Cohen-f effect size of 0.26, confident level of 95%, significant level of 5%, and statistical power of 80% is applied.

Since a 10% dropout rate is anticipated, a total of 36 participants will be needed for this study. Of this total, 18 patients will be allocated to the RM group (RMG) and 18 patients to the MCPJ blocking group (MCPJBG).

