### 3.7 Study Duration and Timeline

Stage 1, review of article 12 months

Stage 2, data collection and data analysis 24 months

Stage 3, presentation and publication 12 months

Each patient will be involved in this study for 8 weeks. The duration of complete recruitment of 36 patients is estimated to be 2 years.

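### The synopsis gives a sample size of 42, while sections 3.6 and 3.7 derive and recruit 36, and nothing in the protocol accounts for the six extra participants

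*Protocol*

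**What the plan says.** The Research Synopsis gives the sample size as "42 participants", with no derivation and no reference to another section.

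Section 3.6 gives the only calculation. It takes pre- and post-treatment pain scores from an earlier trigger-finger study, obtains Cohen's d and converts it to f. It then states: "This proposed study will need 32 participants when a Cohen-f effect size of 0.26", with "significant level of 5%, and statistical power of 80% is applied". After a 10% dropout allowance, "a total of 36 participants will be needed for this study", divided into 18 per arm.

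Section 3.7 repeats that total: "The duration of complete recruitment of 36 patients is estimated to be 2 years".

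Section 3.5 says that withdrawn participants are not replaced, because "we have already included the dropout rate (10%) into our sample size calculation".

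**The concern.** Both 42 and 36 are presented as the total for the same study, and nothing links them. The synopsis row is complete and legible, and no redaction or amendment note explains the difference.

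The planned total is the number against which completion is judged. An ethics committee or a later reader could not tell whether a trial that ended at 36 stopped early, or whether one that ended at 42 over-recruited. The setting gives this some weight. Section 3.8 says the researcher is not blinded, and section 3.15 gives access to the data to the researcher alone. That person could stop at either number and point to a place in the protocol that supports it.

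**Working it through.** **Inputs.** From section 3.6: mean pain 4.65 (SD 2.39) before and 3.40 (SD 2.44) after treatment; f rounded to 0.26; alpha 0.05; power 80%; dropout 10%. From section 3.9: a two-way mixed ANOVA, here with 2 groups and m = 2 measurements (Day 1 and Week 6). The correlation between measurements, ρ, is not stated; 0.5 is assumed.

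**Reproducing 36.**

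1. Effect size: d = (4.65 − 3.40) / √[(2.39² + 2.44²)/2] = 1.25 / 2.415 = 0.518, and f = d/2 = 0.259. Both agree with section 3.6.
2. Sample size for the group-by-time interaction, from the noncentral F with λ = f²·N·m/(1 − ρ). At N = 32, λ = 0.26² × 32 × 2 / 0.5 = 8.65 and power is 0.812. At N = 30, power is 0.785. With equal arms, the smallest N that reaches 80% is 32, as stated.
3. Dropout: 32/0.9 = 35.6, rounded up to 36, or 18 per arm. The cruder 32 × 1.1 = 35.2 also rounds up to 36.

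**Trying to reach 42.**

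- From 32, dropout would have to be 1 − 32/42 = 0.238, about 24%. With the cruder formula it would be about 30% (32 × 1.3 = 41.6). The protocol states 10%.
- At 10% dropout, 42 × 0.9 = 37.8, so about 38 would remain rather than 32.
- 90% power with no dropout allowance gives N = 42, but the protocol states 80% power and 10% dropout.
- ρ = 0.4 gives N = 38, and 38 × 1.1 = 41.8, rounded up to 42 (38/0.9 = 42.2 rounds up to 43). The protocol states neither that correlation nor an N of 38.
- Replacement of withdrawals cannot supply the extra six, because section 3.5 excludes it.

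**Size of the gap.** 42 − 36 = 6, and 6/36 = 16.7%.

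**Sensitivity to ρ.** N before dropout is 44 at ρ = 0.3, 38 at 0.4, 32 at 0.5 and 26 at 0.6. Of these values only 0.5 returns the protocol's 32.

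**Power at each total** (f = 0.26, ρ = 0.5):

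| N analysed | Power |
|---|---|
| 32 (36 less 10%, rounded) | 0.812 |
| 36 | 0.858 |
| 38 (42 less 10%, rounded) | 0.877 |
| 42 | 0.908 |

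**Illustration only.** Suppose one outcome were tested at 36 and, if not significant, tested again at 42, each time at two-sided 5%. The two test statistics would correlate at √(36/42) = 0.926, and the normal approximation gives an overall type I error of 0.068. Simulating 200,000 null trials with a two-sample t-test at 18 and then 21 per arm also gives 6.8%.

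**The case against.** The strongest reply is that the 42 is one unexplained cell in a synopsis, while the body agrees with itself throughout: 32, then 36, then 18 per arm, then recruitment of 36, with dropout already counted. A stale synopsis figure is at least as likely as a second target. That is fair, and it is why the point is a disagreement between synopsis and body. The calculation in section 3.6 is not in error. But the reply does not show which total was approved, and the two still differ.

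A reader might infer more than the text supports in four ways:

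- **That the protocol allows recruitment to go on from 36 to 42 after a look at the data.** It does not. No section plans an interim test or an extension.
- **That the type I error is therefore about 6.8%.** That figure depends wholly on a look that nobody has planned, and it concerns one outcome only. It shows what a single fixed total would guard against and does not describe this design.
- **That the smaller total leaves the trial underpowered.** On the protocol's own effect size and the assumed correlation, both totals exceed 80% power, also after 10% loss.
- **That the contradiction leaves the envelope supply undefined.** Section 3.6 states 18 per arm, and 21 per arm appears nowhere. Section 3.8 gives no envelope count, but it would be absent even if the totals agreed, so that is a separate matter.

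**Conclusion.** The contradiction stands. The planned enrolment total is 42 in one place and 36 in two others, a gap of six participants (17%), and only 36 has a derivation. That 42 does not follow from the stated 32, 10% dropout and no replacement is plain arithmetic and needs no assumption. Reproducing the 32 itself, and the power figures, rests on ρ = 0.5 and on taking the protocol's effect size as given; whether a before-and-after effect suits a comparison between groups is a different question and is not judged here.

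What is at stake is a planned number that cannot be verified: stopping at 36 or at 42 could each be called completion to plan. The discrepancy does not in itself cost power or raise the error rate. It is still wrong as written in a figure the trial relies on, and should be corrected.

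**What to change.** State one total in the synopsis and in sections 3.6 and 3.7.

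- If 36 is the approved total, change the synopsis to 36 (18 per arm). This is one corrected figure.
- If 42 is the approved total, change sections 3.6 and 3.7 to 42 (21 per arm) and give the inputs that produce it: power, dropout allowance and assumed correlation. Bring the 10% in section 3.5 into line if the allowance changes.

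In either case, add one sentence saying that recruitment ends at that number irrespective of results. The first route costs a minor amendment. The second also needs the calculation to be rewritten. Neither alters the design or the visits.

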## **1.0 BACKGROUND AND SIGNIFICANCE**

### **1.1 BACKGROUND**

Trigger finger (TF), or the stenosing tenosynovitis describes disproportionate size of a flexor tendon and tendon sheath at the first annular pulley (A1) at the metacarpophalangeal joint (MCPJ) (Lunsford et al. 2017). It is a common condition of the hand thought to be caused by inflammation or thickening of the tendon tissues that interferes with gliding of the tendon, which may in turn cause pain, clicking, catching and loss of motion (Makkouk et al. 2008). In the early stages, there may be local tenderness and swelling and with time a discrete nodule may form in the area of the A1 pulley (Gil et al. 2020). In severe cases, the affected finger can lock in flexion or extension and cause sharp pain when the finger is actively or passively unlocked. Although the cause of TF is unclear, there is a higher prevalence among people with metabolic diseases such as diabetes mellitus, hypothyroidism, mucopolysaccharidosis, and other inflammatory arthropathies (Gil et al. 2020). In adults the incidence of TF is 28:100,000 per year with a 2.6% lifetime incidence of TF in adults (Akhtar et al. 2005), and a higher prevalence in adult diabetics of between 5% and 20% (Kuczmarski et al. 2018). TF is reported to be more common in middle-aged individuals and women are six times more likely to develop TF than men (Akhtar et al. 2005).

TF can affect hand functions which include precision of work, speed of hand performance, gross power grip, 3-jaw chuck pinch, and manipulation, causing difficulties in performing daily activities (Langer et al. 2017; Lunsford et al. 2017). Poor hand function in people with TF has been reported to contribute significantly to disability (Langer et al. 2016). Financially, treatment of TF by steroid injection or surgery is expensive as pointed out by Zhuang et al. (2020) who compared costs for two different health insurance payers in the United States of America. The cost of a single steroid injection was between \$75.57 (commercial) and \$49.26 (Medicare) and the cost of surgery was between \$902 (commercial) and \$853 (Medicare), respectively. Given that the success rate of a single steroid injection for TF was reported to be about 50%, half of all patients will either have a second injection or will have surgery recommended (Zhuang et al. 2020).

Hand therapy offers a non-invasive and easily accessed first line intervention option for management of TF. Usual therapy management consists of a custom-made splint, hand activity modification with or without nonsteroidal anti-inflammatory medications (Ryzewicz & Wolf 2006). As a result of a Delphi European consensus published in a 'Guideline for Managing Trigger Finger' (Huisstede et al. 2014) three interventions and the order of use were suggested based on the evidence available in 2014. The consensus was that the initial intervention be splint wear, the second intervention a corticosteroid injection, and the third, proceed to surgery. In addition, the level of intervention chosen must take into consideration the severity, duration, and previous intervention history of the individual's TF.

The primary purpose of a splint to manage TF is to limit flexor tendon excursion through the A1 pulley (Evans et al. 1988). To limit tendon excursion, various hand-based and finger-based splints have been described. These splints usually immobilize one finger joint, either the MCPJ, proximal interphalangeal joint (PIPJ), or distal interphalangeal joint (DIPJ). The MCPJ blocking splint appears to be the most frequently used (Colbourn et al. 2008; Driksingen et al. 2017; Evans et al. 1988; Lindner-Tons & Ingell 1998; Patel & Bassini 1992; Tarbhai et al. 2012; Teo et al. 2018; Valdes et al. 2012). One publication immobilized the PIPJ (Teo et al. 2018) and two studies immobilized the DIPJ (Rodgers et al. 1998; Tarbhai et al. 2012). Tarbhai et al. (2012) compared a MCPJ blocking splint with a DIPJ blocking splint noted that the MCPJ blocking splint was preferred, with reasons cited as

being more stable, more comfortable, and less feeling of stiffness. Specifically, unlike DIPJ blocking splint that easily slipped off the finger, the MCPJ blocking splint allowed individuals with TF to perform tip-to-tip prehension which is important for hand function. The PIPJ blocking splint is the least studied splint for management of TF (Teo et al. 2018), which may be due to fabricate and fit issues.

Hand-based splints have been mainly advocated in the literature (Evans et al. 1988; Patel & Bassini 1992; Lindner-Tons & Ingell 1998). Evans et al. (1988) suggested a volar hand-based static splint with the MCPJ immobilized in neutral or 0° with the interphalangeal joints (IPJ) free. These authors hypothesized that wear of the TF splint would: 1) reduce the internal pressure about the A1 pulley; and 2) increase differential glide between the flexor tendons. In their study of 55 digits with TF, symptoms were resolved in 29 digits (52%) and symptoms improved in 12 digits (21%). Patel and Bassini (1992) immobilized 50 fingers in a hand-based splint that immobilized the affected finger's MCPJ in 10° to 15° of flexion leaving the IPJ free for six weeks, with 33 fingers (66%) cured.

Lindner-Tons and Ingell (1998) referred to their hand-based MCPJ blocking splint as a minimal-profile splint design as it covers only the palmar aspect of the MCPJ of the involved finger and is secured by a ring around the finger's proximal phalanx. These authors projected that this splint would appeal to patients because it was less bulky, allowed for unrestricted hand function and cosmetically, and that these attributes might improve splint wear adherence and subsequently outcomes. Others have since adopted Lindner-Tons' splint design for their research (Colbourn et al. 2008; Drikoningen et al. 2017; Tarbhai et al. 2012; Teo et al. 2018; Valdes et al. 2012).

The relative motion (RM) splint is a finger-based design that holds potential for management of TF. The relative motion extension (RME) splint plus a wrist splint was originally used to manage extensor tendon repairs (Merritt 1998). Howell et al. (2005) (N=140) showed the RME splint to be protective, with no tendon ruptures and no active finger extension lags in 81% of the patients and allowed mobility as 79% of the patients had no loss of finger flexion. Because of the low profile, small size, and mobility afforded by the splint, patients were able to return to work in an average of 18 days post repair (Howell et al. 2005). In 2011, Hirth et al. had compared use of a RME splint without the wrist splint to management of zone V-VI extensor tendon repairs by immobilization for 4 weeks (Hirth et al. 2001). They too reported the benefits of the RME splint to be more cost effective, easy to fabricate, more convenient to wear, and allowed patients to return to work earlier than immobilization.

Historically the primary purpose of any splint designed to manage TF has been to block the MCPJ, PIPJ and/or DIPJ to reduce flexor tendon excursion, hence tendon/sheath irritation by the A1 pulley (Colbourn et al. 2008; Drikoningen et al. 2017; Evans et al. 1988). The MCPJ blocking splint used in this study is intended to completely stop MCPJ motion and the RM splint to constrain MCPJ motion by at least 20-25°. It is unclear if the quadriga effect attributed to RM splint used after tenorrhaphy has a role in the treatment of TF. From biomechanical studies, we understand that the quadriga effect is levied by a RME splint to protect extensor tendons repairs in zone VI (Sharma et al. 2006) and by the RMF splint for flexor digitorum profundus (FDP) tendon repairs in zone III (Chung et al. 2017). The quadriga effect has been documented to be possible when multiple tendons are controlled by a single muscle, such as the extensor digitorum communis (EDC), FDP, and in the presence of tendinous interconnections of the extensor indicis proprius (EIP) and extensor digiti

minimi (EDM) to the EDC-multi-tendon unit (Henry et al. 2020; Hirth et al. 2011; Howell et al. 2005; Merritt 2014). As a result, when the affected finger's MCPJ is positioned in relatively greater extension or flexion, the active force is diverted more to the other tendons than the affected tendon (Merritt 2014). This principle of RM has been proven to protect repairs of the EDC, EIP, EDM in zones IV-VII and FDP in zones I-II (Henry et al. 2020; Hirth et al. 2011; Howell et al. 2005; Merritt 2014). It is unknown the role of quadriga in the management of other hand conditions such as sagittal band rupture (Catalano et al. 2006; Peelman et al. 2014), boutonniere deformity (Merritt & Jarrell 2020), digital nerve repair (Hirth et al. 2016) or undiagnosed hand pain (Lalonde 2013). Likewise, clinical experts reported use of the RM splint to manage TF (Hirth et al 2016). Yet, there is no evidence as to why the splint has worked.

For this study, we propose the following operational premises as to why a RM splint may work in the management of TF involving the A1 pulley. During controlled active motion: 1) the RME splint will lessen the passive tension of the extensor tendon(s) of the affected TF (quadriga), which biomechanically should lessen the force of flexion on the A1 pulley; 2) the RMF splint will levy the quadriga effect on the FDP to lessen the force generated and tendon excursion, and allow full FDS excursion (Savage 1988) and 3) the RME and RMF splints will decrease the amount of total active flexor tendon excursion by at least 25° without fully blocking MCPJ motion to support tendon healing (Evans et al. 1988).

The RM splint is a finger-based splint that is low profile, allows for a wide range of finger motion, permits unrestricted hand function with patients reporting greater satisfaction (Collocott et al. 2020; Hirth et al. 2016; Newington et al. 2021). TF may occur in one or multiple digits to which a RM splint can be adapted. Since TF involves primarily the flexor tendons, it is postulated that RM splint that positions the affected finger's MCPJ in relatively more flexion or extension will divert the tension of tendon to adjacent tendon and subsequently limit tendon excursion of the involved finger through A1 pulley. Since the RM splint reallocates the forces, but does not immobilize, protected active movement can be continued, and tendon healing supported. The design of the RM splint to be used when treating TF can be determined by first using the RM Pencil Test (Lalonde 2017) which simulates the RME or RMF position. The position that stops or reduces the patient's pain/triggering, determines which splint to fabricate and the degrees of difference between MCPJ to incorporate.

